## Interventions

### Procedures

The ENDOANGEL-GC is an AI system designed for assisting in EGD and possesses three functions in real time: (1) to time the entire procedure (from the endoscope intubating into the mouth to it being drawn out), (2) to record observed upper gastrointestinal tract landmarks and blind spots, and (3) to mark the upper gastrointestinal lesion with a blue rectangular box (box colour turns red if the lesion is predicted to have a high risk of gastric neoplasm) [16, 17].

The ENDOANGEL-GC is connected to the endoscopy processor, receives digital images as input, and outputs the predictions of landmark monitoring and lesions. The ENDOANGEL-GC is installed on a separate computer system, and the output of the system appears on the same monitor as that of the endoscope. A button on the system is set to switch between “assistance” and “no assistance” modes. Before examination in the control group, the ENDOANGEL-GC is shifted to the “no assistance” mode, so the predictions will be concealed, as they are not displayed on the monitor. Before the examination in the experimental group, the ENDOANGEL-GC is shifted to the “assistance” mode, so the predictions and prompts are displayed on the screen.

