The endoscopists who participate in the study are required to have EGD experience with more than 500 cases. All participating endoscopists will be trained in the AI’s functions, including monitoring anatomical landmarks, detecting suspicious lesions, and becoming familiar with the operation requirements during endoscopy. Each endoscopist will perform at least 10 examinations with AI assistance. In both groups, endoscopists are required to screen the entire stomach under white light mode. Only when the screening process is completed and suspicious lesions are found, the image-enhanced mode will be allowed for further judgement. In the experimental group, the endoscopists will operate the endoscope with the assistance of ENDOANGEL-GC. They are required to adhere to the following criteria: (1) screen anatomical landmarks according to the feedback of ENDOANGEL-GC and (2) lesions marked in red boxes by ENDOANGEL-GC are required to undergo biopsy sampling. Lesions that are not marked in red boxes but meet any of the following criteria are also recommended for biopsy: differences in colour, loss of vascularity, slight elevation or depression, nodularity, thickening, abnormal convergence or flattening of folds, irregular margins, irregular discoloration, or irregular surfaces. In the control group, endoscopists will routinely operate on the endoscope. Lesions that meet the above criteria are also recommended for biopsy.

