### Data collection

Data will be collected in a standard case-report form through the EDC system and anonymised for further analysis. Data include baseline information, endoscopic reports, and pathological results. Data will be de-identified before being entered into the database. Regular quality monitoring and database checking will be performed at each centre to ensure data accuracy.

In addition, the computer on which the ENDOANGEL-GC runs will be equipped with video-recording software. It is used to capture and store video signals from the endoscope device and predictions from the ENDOANGEL-GC system. For each examination, an unprocessed raw video from the endoscope and a video with ENDOANGEL-GC predictions (“AI” videos) are recorded and stored.

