### Data analysis plan

The analysis will use intention-to-treat (ITT) and PP approaches. The ITT population will include all patients who are randomised, whereas the PP population will include patients who undergo EGD in accordance with the assigned intervention. The null hypothesis is that the detection rates of gastric neoplasms and EGC in the experimental group will not differ from those in the control group. An alternative hypothesis is that the detection rates of gastric neoplasms and EGC in the experimental group will differ from those in the control group. The experimental group (with ENDOANGEL-GC assistance) will be compared with the control group (without ENDOANGEL-GC assistance) for the two primary outcomes using the *χ*^2^ test.

Continuous variables will be expressed as means (standard deviations [SDs]) or medians (interquartile ranges [IQRs]), according to their distributions, and categorical variables will be presented as numbers (percentages). Baseline characteristics between the two groups will be compared using the *χ*^2^ test for categorical variables and the Mann-Whitney *U* test for continuous variables. Statistical significance is set at *p* < 0.05. A 95% confidence interval will be calculated. Subgroup analysis will be conducted, stratified by multiple indices, such as age and ENDOANGEL-GC-marked red boxes, indicating that only red-box-marked lesions will be included in the analysis. The histological data and lesion characteristics will be compared with the ENDOANGEL-GC prediction, and the performance of ENDOANGEL-GC will be further analysed.

In this study, the potential missing data include the following: (1) characteristic information (the missed data will be marked with “NA” and will not be included in the analysis); (2) pathological results, the gold standards for analysis (participants with missing pathological results are excluded from the analysis); and (3) original videos (the data contained information on whether the endoscopic procedure adhered to the protocol requirements). Participants without this information will be excluded from the per-protocol analyses.

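### The red-box subgroup selects lesions on a mark that arises after randomisation and forces biopsy in one arm only, so it is not a valid between-arm subgroup; sensitivity from the same data would need care

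*Protocol article*

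**What the plan says.** The subgroup sentence in the Data analysis plan reads "stratified by multiple indices, such as age and ENDOANGEL-GC-marked red boxes, indicating that only red-box-marked lesions will be included in the analysis", so the mark stands beside age as a stratifying index. Shortly after, the section adds a performance analysis: "The histological data and lesion characteristics will be compared with the ENDOANGEL-GC prediction". It names no metric and no arm.

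The Procedures section gives the mark different roles in the two arms:

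- Experimental arm, marked lesions: "lesions marked in red boxes by ENDOANGEL-GC are required to undergo biopsy sampling".
- Experimental arm, unmarked lesions: "Lesions that are not marked in red boxes but meet any of the following criteria are also recommended for biopsy". A list of visual features follows.
- Control arm: the system runs in a silent mode, "so the predictions will be concealed, as they are not displayed on the monitor". For biopsy, "Lesions that meet the above criteria are also recommended for biopsy".

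The mark is nevertheless recorded in both arms. Under Data collection the article says: "For each examination, an unprocessed raw video from the endoscope and a video with ENDOANGEL-GC predictions" are stored. A red-box comparison between arms is therefore feasible.

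Three further rules bear on verification. Participants whose pathology is missing leave the analysis (Data analysis plan). Lesion frames for expert review are captured only where pathology exists (Specimen management and pathological traceability). A red-box lesion left without pathology leads to per-protocol exclusion in the experimental arm only (Adherence and protocol deviations).

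**The concern.** A subgroup comparison keeps the protection of randomisation only if the subgroup is defined by something the intervention cannot affect. Age meets that condition. The red box does not, for two reasons.

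First, a box depends on what the endoscope is shown. Experimental-arm endoscopists must follow the system's feedback on landmarks, so the set of marked lesions may differ between arms because of the intervention itself.

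Second, the mark determines whether the reference standard is obtained in one arm and not in the other. Marked lesions should have near-complete pathology in the experimental arm and selective pathology in the control arm.

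The second feature also affects the performance analysis. In the experimental arm a positive prediction compels verification, while a negative one leaves it to a recommendation. A missed neoplasm is then less likely to be counted than a marked one. At stake are a subgroup result that could mislead in either direction and, if sensitivity is reported, an estimate that flatters the system.

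**Working it through.** The article gives no figure for either analysis, so there is none to reproduce. Its sample-size figures do not bear on the point. All biopsy rates, prevalences and sensitivities below are assumptions. The one value with a link to the article is 62.5%, the ratio of the planned neoplasm detection rates, 2.5% / 4.0%, used purely as an illustration.

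**1. Comparison among red-box lesions**

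Let π be the share of red-box lesions that are neoplastic, taken as equal in both arms. Let b1 and b0 be the control-arm biopsy probabilities for neoplastic and benign red-box lesions. Biopsy of marked lesions in the experimental arm is taken as complete.

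- Experimental yield = π.
- Control yield among red-box lesions with pathology = π·b1 / [π·b1 + (1 − π)·b0].
- The control yield exceeds π exactly when b1 > b0.

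With 1,000 red-box lesions per arm, 100 of them neoplastic, b1 = 0.70 and b0 = 0.40:

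- Experimental: 100 / 1,000 = 10%.
- Control: (0.70 × 100) / (0.70 × 100 + 0.40 × 900) = 70 / 430 = 16.3%.

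The experimental arm confirms 30 more neoplasms and yet shows the lower yield. The range, with π = 0.20 and b1 = 0.625 (experimental yield 20.0%):

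| b0 | Control yield, lesions with pathology |
|---|---|
| 0.2 | 43.9% |
| 0.4 | 28.1% |
| 0.625 | 20.0% |
| 0.8 | 16.3% |

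At b0 = 0.4, control against experimental is 14.8% against 10% for π = 0.1, and 61.0% against 50% for π = 0.5.

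If every red-box lesion stays in the denominator, the control yield is π·b1. In the worked example that is 70 / 1,000 = 7% against 10%. With π = 0.20 and b1 = 0.625 it is 12.5% against 20.0%. Neither case reverses. With equal numbers randomised per arm, counts per randomised patient keep the same order, 70 against 100. The all-lesions version still relies on π being equal in both arms, which the prompts could disturb; the per-patient denominator does not condition on the mark.

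**2. Sensitivity, if it is reported**

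Let S be true sensitivity among neoplasms viewed and v the share of unmarked neoplasms that get pathology, with marked ones fully verified.

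Apparent sensitivity in the experimental arm = S / [S + (1 − S)·v]. For S = 0.80:

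- v = 0.625: 0.80 / 0.925 = 86.5%
- v = 0.50: 0.80 / 0.90 = 88.9%
- v = 0.25: 0.80 / 0.85 = 94.1%

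Pooling both arms equally, with 62.5% of marked neoplasms verified in control and v the same in both arms, the marked and verified share is 0.80 × (1 + 0.625) / 2 = 0.65:

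- v = 0.625: 0.65 / (0.65 + 0.125) = 83.9%
- v = 0.25: 0.65 / (0.65 + 0.05) = 92.9%

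Control arm alone, 0.50 / (0.50 + 0.20·v):

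- v = 0.625: 80.0%, unbiased because marked and unmarked neoplasms are verified equally often
- v = 0.50: 83.3%
- v = 0.25: 90.9%

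At each v the control arm is closest to the truth, but it is exact only if biopsy of a neoplasm is unrelated to the hidden mark.

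**The case against.** A reader might infer that the planned comparison will reverse and that the article's estimate of sensitivity is overstated. The documents do not support either as a fact.

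- **Denominator.** The reversal needs red-box lesions with pathology as the denominator, and the article does not fix one for this subgroup. Under Outcomes, the neoplasm detection rate is taken over the recruited population. Carried into the subgroup, that would mean red-box neoplasms per recruited patient, where the example does not reverse. The missing-pathology rule works on participants, and nothing says that an unbiopsied lesion counts as a missing result. This objection stands.
- **Metric and arm.** The article speaks of performance, not sensitivity, and does not confine the analysis to the experimental arm. Positive predictive value in that arm is much less affected, because marked lesions are to be biopsied. This also stands, so the sensitivity point is conditional.
- **Size of the gap.** The same visual criteria guide biopsy of control-arm lesions and of unmarked experimental-arm lesions, and the list is broad. The gap between required and recommended biopsy may be smaller than assumed here. It is unknown from the article.
- **Detail left to an analysis plan.** Denominators and metrics are commonly fixed there. Selecting lesions on the red box as a subgroup factor, however, is a rule the article states, and choosing a denominator does not turn the mark into a baseline variable.

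**Conclusion.** The point holds in a limited form. A between-arm comparison restricted to red-box lesions is not a valid randomised subgroup: the mark arises after randomisation, the prompts can change it, and it compels biopsy in one arm only. This follows from the article's own rules and needs no assumed number.

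The size is conditional. Reversal occurs only among red-box lesions with pathology, and only if control endoscopists biopsy neoplastic red-box lesions more often than benign ones. Overstated sensitivity arises only if sensitivity is estimated from the experimental arm or from pooled data, and only to the extent that unmarked neoplasms are verified less often than marked ones. None of the rates behind the illustrations can be recovered from the article.

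The consequence is confined to the subgroup and performance analyses. The primary intention-to-treat comparison does not select on the mark and is not touched by this point.

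**What to change.** Change the analysis wording as follows; the biopsy rules themselves need no change for this purpose.

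1. Restrict between-arm subgroups to variables fixed before randomisation, such as age, indication, *H. pylori* status and centre.
2. Report red-box-marked neoplasms descriptively by arm, as counts per randomised patient, and do not present them as a treatment-effect subgroup.
3. Report the system's performance separately by arm. Base sensitivity primarily on the control arm's concealed predictions. Give the number of marked and unmarked lesions without pathology, and a range for verification bias, because the visual features that prompt biopsy may correlate with the hidden mark.

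No new data are needed, since prediction videos are stored for every examination. The cost is the matching of control-arm marks to biopsied lesions on those videos, together with fewer verified lesions and less precision for the performance estimate.

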With the rapid progress in artificial intelligence (AI) technology, several researchers have developed intelligent systems aimed at diagnosing EGC or upper gastrointestinal neoplasms, and few studies have aimed to ensure the completeness of examinations [14, 15]. In 2019, we first applied deep learning algorithms to the field of endoscopy quality control. We developed WISENSE (renamed ENDOANGEL), an intelligent system aimed at monitoring blind spots in upper gastrointestinal endoscopy in real time [16]. Single-centre and multi-centre randomised controlled trials (RCTs) have proven to significantly reduce the blind spot rate in examinations. Furthermore, we developed ENDOANGEL-LD (lesion detection) to detect gastric abnormalities and diagnose gastric neoplasms (low-grade dysplasia, gastric adenomas, gastric lymphomas, EGC, and advanced gastric cancers) in real time [17]. In another single-centre, tandem-designed trial, we proved that ENDOANGEL-LD could reduce the biopsy rate and miss rates of gastric neoplasms in real time [18].

Development of a tool with the ability to simultaneously improve the diagnostic performance of WLE and ensure high completeness of examination is an ideal way to fulfil these needs. Therefore, we proposed the AI system ENDOANGEL-GC (gastric cancer), which simultaneously combines the functions of blind spot monitoring and lesion detection and runs in real time. We designed this randomised, controlled, patient-blinded, multi-centre trial with two parallel groups and a 1:1 allocation to evaluate the hypothesis that ENDOANGEL-GC would improve the detection rates of gastric neoplasms and EGC.

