## Outcomes

The primary outcome measures are detection rate of gastric neoplasms and EGC detection rate. The gastric neoplasm detection rate is defined as the ratio of patients with neoplasms to the recruited population. The EGC detection rate is defined as the ratio of patients with EGC to all patients with gastric cancer. EGC includes pathologically proven high-grade intraepithelial neoplasia and gastric cancer restricted to the mucosa and submucosa.

Secondary outcome measures include the detection rate of premalignant gastric lesions, biopsy rate, observation time, and number of blind spots on EGD examination. The detection rate of premalignant gastric lesions was defined as the ratio of patients with premalignant gastric lesions to the entire recruited population. The biopsy rate is defined as the ratio of patients who undergo biopsy in the recruited population. The observation time is defined as the overall examination time under WLE minus the biopsy operation time. Blind spots are defined as unobserved landmarks.

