## Study withdrawal

Eligible participants will be included in this study after providing informed consent and undergoing randomisation. The participants can withdraw at any time during the study. Data collected prior to withdrawal can be used in this study if informed consent is obtained. Participants should be withdrawn in the following situations: (1) perforation, (2) massive haemorrhage, (3) allergy to sedative medication, (4) poor preparation, and (5) gastric retention. Withdrawn participants will not be replaced by other recruited participants after they sign the informed consent form.

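### The missing-pathology exclusion is not limited to the per-protocol set, so it contradicts the ITT definition and the recruited-population denominator and selects on a post-randomisation variable

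*Protocol article*

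**What the plan says.** The Data analysis plan promises ITT and PP analyses and defines the first without exception: "The ITT population will include all patients who are randomised". Its paragraph on missing data then gives a rule for pathology: "participants with missing pathological results are excluded from the analysis". The item that follows, on missing videos, is explicitly restricted: "Participants without this information will be excluded from the per-protocol analyses". The pathology item has no such restriction.

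The Outcomes section fixes the denominators. For the first primary outcome: "The gastric neoplasm detection rate is defined as the ratio of patients with neoplasms to the recruited population". For the second: "The EGC detection rate is defined as the ratio of patients with EGC to all patients with gastric cancer". It also makes biopsy a secondary outcome: "The biopsy rate is defined as the ratio of patients who undergo biopsy in the recruited population".

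Three other places bear on the point:

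- **Interventions, Procedures.** Red-box lesions must be biopsied in the experimental arm. Lesions meeting the listed visual criteria are only recommended for biopsy, in both arms.
- **Adherence and protocol deviations.** A red-box lesion with no pathology is a PP exclusion, in the experimental arm only.
- **Specimen management and pathological traceability.** Resection pathology is traced for 60 days to establish invasion depth.

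**The concern.** For the neoplasm outcome the three statements cannot all be followed. If a randomised patient lacks a pathology result, the ITT definition and the outcome definition keep that patient in the denominator, and the missing-data rule takes the patient out. Because PP carries the same exclusion, neither planned analysis is clearly free of it.

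The exclusion also acts on something that happens after randomisation and can differ by arm. Tissue is taken by endoscopists who know the allocation, and one trigger for mandatory biopsy exists in one arm only. The Introduction reports of the predecessor lesion-detection system that "ENDOANGEL-LD could reduce the biopsy rate and miss rates of gastric neoplasms in real time", so the investigators themselves regard biopsy frequency as something such a system may change. An unrestricted rule would also carry the one-sided PP deviation for red-box lesions without pathology into ITT. At stake is whether the comparison on a primary outcome keeps the protection of randomisation.

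**Working it through.** **1. The plan's own figures.** For a two-sided α of 0.05 and 80% power, n per arm = [1.96·√(2p̄(1−p̄)) + 0.84·√(p₁(1−p₁)+p₂(1−p₂))]² / (p₁−p₂)².

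- Neoplasm, 2.5% vs 4.0%: 2,193 per arm, 4,386 in total, 4,874 after dividing by 0.9 (rounded up per arm). The unpooled variance gives 4,868. The plan has 4,858.
- EGC, 20% vs 35%: 276 cancers pooled, 272 unpooled. The plan has 270, and 270/0.01/0.9 = 30,000.

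The sample sizes reproduce closely. The problem is not one of arithmetic.

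**2. Set-up for the exclusion rule.** Assume no true effect: 2.5% of randomised patients (the plan's control rate) have a detected neoplasm in each arm. With 30,000 patients allocated 1:1 there are 15,000 per arm, hence 375 detected per arm. If a share m of an arm is dropped, none of them with a detected neoplasm, the observed rate is 0.025/(1−m). The chance of p < 0.05 is approximately Φ(|d|/SE − 1.96) + Φ(−|d|/SE − 1.96), where d is the difference in observed rates. With nobody dropped it is 5.0%. The documents give no biopsy or missingness rates, so all those below are assumed.

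**3. Narrow reading: a result was due but is unavailable.** Worked case, 5% dropped in the experimental arm only: 375/15,000 = 2.50% and 375/14,250 = 2.63%; d = 0.00132, SE = 0.00185, ratio 0.71, chance 11%.

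| Dropped, control vs experimental | Observed rates | Chance of p < 0.05 |
|---|---|---|
| 0.8% vs 0.6% (2% of results lost, biopsy rates 40% and 30%) | 2.52% vs 2.52% | 5.0% |
| 4% vs 3% (10% of results lost, same biopsy rates) | 2.60% vs 2.58% | 5.2% |
| 0% vs 2% | 2.50% vs 2.55% | 5.9% |
| 2% vs 5% | 2.55% vs 2.63% | 7.2% |
| 0% vs 5% | 2.50% vs 2.63% | 11% |
| 5% vs 10% | 2.63% vs 2.78% | 12% |
| 0% vs 10% | 2.50% vs 2.78% | 31% |

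The first two rows have equal loss per biopsy. The others have loss that differs by arm.

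**4. Broad reading: non-biopsied patients also count as missing.** The observed rate becomes 0.025 divided by the biopsy rate. Worked case, 40% vs 38%: 375/6,000 = 6.25% and 375/5,700 = 6.58%; d = 0.00329, SE = 0.00453, ratio 0.73, chance 11%.

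| Biopsy rate, control vs experimental | Observed rates | Chance of p < 0.05 |
|---|---|---|
| 40% vs 38% | 6.25% vs 6.58% | 11% |
| 40% vs 36% | 6.25% vs 6.94% | 32% |
| 40% vs 35% | 6.25% vs 7.14% | 47% |
| 40% vs 44% | 6.25% vs 5.68% | 27%, against AI |

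**5. EGC.** The denominator is patients with gastric cancer, so the recruited-population conflict does not arise. The exclusion can still distort the ratio if confirmed cancers without resection pathology are treated as missing. If a share f of non-early cancers is dropped and no early ones, a true 20% becomes 0.20/(0.20 + 0.80(1−f)): 23.8% at f = 20% and 33.3% at f = 50%. Both values of f are assumed.

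**The case against.** The strongest reply is that missing plainly means a result that should exist but does not. The rule stands beside lost baseline items and lost videos. Biopsy rate is an outcome measured over all recruits, so having no biopsy is an expected state. The sample size allows for only 10% dropout, whereas dropping everyone without a biopsy would discard 60–70% of patients at biopsy rates of 30–40%. This is persuasive. A reader might infer that the primary outcome turns into neoplasms per biopsied patient and that a false positive is nearly certain; at assumed biopsy rates of 40% vs 30% the chance would be about 98%. The documents do not support that as the expected consequence: it needs the less natural reading and a gap between arms that no stated figure backs.

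The direction is also open. The reported reduction in biopsies comes from a predecessor system in a single-centre tandem trial, and mandatory red-box biopsy could push the rate up instead.

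A reader might further infer from the Study withdrawal section ("Participants should be withdrawn in the following situations") that the unblinded operator removes patients from ITT. The section names neither who decides nor any effect on the denominator, and it allows earlier data to be used with consent. It is a gap to close, not evidence of bias.

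Finally, sensitivity analyses are normally left to an SAP, which is not shown, so their absence here is no fault. What survives all of this is the contradiction: even on the narrow reading, randomised patients leave an analysis defined as containing every one of them.

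**Conclusion.** The point holds. The pathology exclusion, as worded, conflicts with the ITT definition in the same section and with the stated denominator of the neoplasm outcome, and it conditions on a post-randomisation variable that can depend on arm. That conclusion needs no assumption about rates.

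The size does. On the more natural reading it is negligible when results are lost at the same rate per biopsy in both arms (about 5%), and modest when 2–10% of patients are dropped unequally (about 6–12%), reaching 31% only at 10% vs 0%. It is large only if non-biopsied patients are also counted as missing. All of these figures assume 15,000 per arm, no true effect and no detected neoplasm among those dropped. It should be corrected because it governs a primary outcome and the correction costs almost nothing.

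**What to change.** **Neoplasm outcome.** Limit the pathology-based exclusion to the PP analysis. In ITT, keep every randomised patient in the denominator of the assigned arm, and count a patient with no biopsy, or with no available result, as no neoplasm detected. Add a sensitivity analysis by arm for lost results; its details can sit in the SAP. State that patients withdrawn under the Study withdrawal section stay in the ITT denominator, subject to consent.

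**EGC outcome.** Keep the denominator of patients with gastric cancer. Do not drop confirmed cancers that lack resection pathology within 60 days. Retain them under one pre-specified classification applied identically in both arms, and vary that classification in a sensitivity analysis.

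**Cost.** A few sentences and the sensitivity analyses, with no extra patients. Detection rates will be slightly conservative where results are lost. The article reports enrolment as ongoing, so the wording should be settled before any comparison by arm.
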